**Methods:**

The evaluation study was designed as a 2-arm randomized trial with 2 phases, each with a 3-week intervention period. In both phases, employees were required to use the app to record daily stress and to wear a wearable sensor to measure heart rate variability. The app offered interventions based on algorithms, which altered the probability of their selection after learning from the data, thereby personalizing the user experience. In the second phase of the study, the sample was divided into 2 groups, varying the degree of personalization of the app. To analyze effectiveness, a 2-factorial mixed within-between design will be applied to compare the outcomes between both groups as well as in a pre-post comparison. In addition, exploratory analyses of the usability of the approach are planned.

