The pathways of the tree were represented by a series of successive questions about the experience of the current stress event. These were answered personally, resulting in increasingly specialized questions until, at the end, an intervention was delivered that was suitable for the input. The possible interventions from the repertoire were not exclusive per pathway, allowing for a wide range of interventions per pathway with different probabilities. The system decided which single intervention to offer the user based on the probabilities. The probabilities could be influenced by how the participants rated the intervention after it had been presented. Consequently, following a sufficient period of use, the probabilities of the interventions should be strongly modified on an individual basis, thereby reflecting the personal preferences for the interventions that are perceived to be personally most effective.

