## Methods

### Study Design

The study used a 2-arm randomized controlled design, comprising 2 experimental groups with varying levels of intervention. In a field design, participants applied the intervention in their natural (occupational) environment. Two 3-week study periods were conducted, with all participants receiving the same intervention in the first 3-week phase (P1) and, after a 3-week break, being allocated to 1 of 2 groups in the second 3-week phase (P2). This resulted in a within-subject comparison in the pre-post design as well as between-subject comparisons between both experimental groups. The within-subject design consisted of the collection of time series data enabled by the continuous daily measurement of variables. Subjective data on experiences and stress levels were collected daily in the morning and evening, as well as at least twice during the day, via the app. Continuous physiological data were also collected via wearing a sensor. In contrast, the between-subject design comprised 3 measurement points: before P1 (T1), between P1 and P2 (T2), and after P2 (T3). At these times, web-based questionnaires about chronic stress and various usability aspects of the wearable app system were submitted via a web-based survey platform. The break was used to improve the mobile app based on user feedback, split the participants into the experimental groups, train the models for automated stress detection based on the HRV and questionnaire data recorded in P1, and implement the weight adjustment mechanisms for personalized intervention delivery.

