From the second week of the study in P1, interventions were triggered on the basis of individual stress information. On the one hand, a trigger was immediately released when (very) high stress was subjectively noted within the daily questionnaires. On the other hand, a trigger was released from objective sensor data. Multiple HRV metrics were calculated from measured sensor data based on 5-minute intervals. A stress intervention was triggered if (1) both the root mean square of successive differences (RMSSD) and the low frequency (LF) to high frequency (HF) ratio exceeded a predefined absolute threshold (deceded for RMSSD; exceeded for LF/HF ratio), (2) both metrics were among the 25% most significant values for the individual within a 24-hour window, and (3) both conditions held for 2 consecutive 5-minute time intervals.

From the trigger, a notification displayed in each area of the app provided access to the decision tree, which used various questions about the circumstances of the current stress experience to offer the optimal individual intervention. The main areas of the decision tree were external stressors, internal stressors, and indirect stress-related areas. For external stressors, the focus was on a dichotomy between occupational and other stressors, while for other stressors, it was noted that the Relax project only addressed occupational stress, so the participants were redirected to the top level of the decision tree. Internal stressors were divided into amplifiers, emotions, reactions, and resilience. The peripheral areas were divided into prevention and further information. All of these areas were further specified by the participants through up to 4 levels of predefined pathways. At the end of each path, there were several possible interventions.

The possible interventions were weighted differently depending on the end point of the pathway. The weights ranged from 0 to 1, with a higher weight increasing the likelihood of allocation. In the preliminary stages of the project, the initial weights were set according to the expert opinion of the development team. After P1, the initial weights for intervention selection were adapted based on all available user interactions. Popular intervention for a specific context received increased weights, thus a higher probability of being chosen in the subsequent context. Within P2, the weights of these mappings were adapted instantly for each intervention feedback.

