The choice of intervention was made automatically by the system on the basis of the random weighted selection. At each node of the pathway, participants had the opportunity to immediately choose the weighted random selection of an intervention.

The 179 interventions were drawn from various areas of CBT, including psychoeducation, skills and attitude training, and relaxation and health habits. The interventions were designed as microinterventions that could be completed in a short period so that they could be easily integrated into everyday work life. Presentation formats varied across interventions depending on their applicability. These included simple text or tables with information, task prompts with a description and call to action, assisted tasks where participants received automated live instructions or otherwise interacted live with the app, or open prompts where participants were given an open field for response and self-reflection. In addition, there were pseudochats where participants were guided through automated educational chat transcripts, audio, or video content. At the end of an intervention presentation, the intervention could be rated. These ratings changed the initial weights of the intervention accordingly. Over time, this resulted in an individualized weight pattern of possible interventions for each person. For economic reasons, the system could not reach the stage at which interventions were offered fully automatically, so participants used the decision tree to receive interventions until the end of the study. Multimedia Appendix 1 illustrates the intervention areas and their subtypes in relation to their initial probability of occurrence with respect to the various stressor types within the decision tree. This higher probability is represented by the presence of an initial weight >0.5 (range from 0.0 to 1.0). In addition, Multimedia Appendix 1 depicts the presentation formats applied to these intervention areas and subtypes, as well as their quantities.

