The level of individualization of interventions in the respective experimental group was characterized by a variation in automatic individualization with regard to the interventions offered by the learning agent. Due to intentionally high α values during the adjustment of the intervention weight matrix, the *local* group had the possibility of significantly influencing their intervention delivery within 3 weeks, while the group *global* would only perceive minor changes. α-local describes the extent to which a rating changed the weight of an intervention for a single user. For the group *global*, it was set to 1.0 (no change to the user’s own weight), and for the group *local*, it was set to 2.1. The weights were adapted using the following formula: new_weight=old_weight * (alpha_local^old_weight). α-global describes the extent to which a rating changed the weight of an intervention for all users. It was set to 21 for both groups. The weights were adapted using the following formula: new_weight=old_weight *(alpha_global^(old_weight/number_of_users)).

Data entry was continuously monitored by the study team throughout the weeks. Participants were encouraged to continue their engagement through regular emails from the study team. It was expected that a general increase in adherence would be achieved as these messages were sent to all participants equally. If technical problems occurred, they were addressed individually via the app and generally via email. It is assumed that such individual correspondences would not add to the overall bias of the user experience since the individual disruption was already a bias, which is not uncommon in pilot studies. In P1, an update of the app was offered in the second week, which solved the technical problems that had arisen up to that point. Participants were given support to reinstall the app, and a self-help guide for the most common technical problems was offered. During the break between P1 and P2, additional technical difficulties were overcome by the study team, and when feasible and relevant, the participants’ input thus far was considered. Following this adaptation of the system in accordance with feedback, a graphical overview of the sensor data was made available in P2. This enabled the participants to maintain awareness of the data and its evolution over time.

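### The article says ratings gave each person an individualized weight pattern, but its own details confine own-rating weighting to the local arm in P2, so the pooled pre-post change is not evidence on it

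*Protocol article*

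**What the plan says.** Three passages describe rating-driven personalization without limiting it to an arm or a phase.

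- App Intervention, after explaining that ratings change the weights: "Over time, this resulted in an individualized weight pattern of possible interventions for each person".
- The Relax Approach section, on what should follow after enough use: "the probabilities of the interventions should be strongly modified on an individual basis".
- Abstract, Methods: "The app offered interventions based on algorithms, which altered the probability of their selection after learning from the data, thereby personalizing the user experience".

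Other passages limit it.

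- Study Design, on P1: "with all participants receiving the same intervention in the first 3-week phase (P1"). The same section lists, among the tasks of the break, to "implement the weight adjustment mechanisms for personalized intervention delivery".
- App Intervention, on the step between the phases: "After P1, the initial weights for intervention selection were adapted based on all available user interactions". Immediate adaptation after each rating is placed within P2.
- Randomization: weights in the local arm depend mainly on the participant's own ratings, and weights in the global arm on the ratings of all participants.
- App Intervention, on alpha-local in the global arm: "it was set to 1.0 (no change to the user"; the sentence continues with that user's own weight. Alpha-local is 2.1 in the local arm. Alpha-global is 21 in both arms, and its exponent is divided by the number of users.

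The Statistical Analysis section plans two things: a comparison between groups, tied to the degree of individualization, and a pre-post analysis of stress over time.

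**The concern.** If every participant ended with a personal weight pattern, a fall in stress across the sample could be read as bearing on individual weight learning. If only one arm in one phase had such weighting, that reading fails, because most of the data behind the pooled change were collected without the feature. The Discussion makes the reading easy: it presents the system as a constantly learning app with content fitted to the individual. The Limitations section names the missing untreated control group, but not this.

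The group comparison is also affected. The Sample Size section refers to main effects, and the measurement points include P1, which precedes allocation. A group main effect averaged over all points would mix the period in which personalization differed with periods in which it could not have differed.

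**Working it through.** The article gives no figure for the share of use under own-rating weighting, so there is none to reproduce. The recommended sample size of 31 plays no part here.

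**1. Who had own-rating weighting, on the specific passages**

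| State | Source of weights | Moved individually by own ratings? |
|---|---|---|
| P1, all participants | Initial expert weights; mechanism not yet implemented | No |
| P2, global arm | Weights adapted from all users, then the alpha-global term only | No, only through the shared term |
| P2, local arm | The same start, then alpha-local 2.1 plus the alpha-global term | Yes |

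**2. Size of one adjustment, from the two printed formulas**

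The multiplier through alpha-local is alpha_local^w. Through alpha-global it is alpha_global^(w/number of users). Take w = 0.5 and 46 users (an assumption; the article does not say which count entered the formula).

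- Local arm, alpha-local: 2.1^0.5 = 1.449, about +45%.
- Global arm, alpha-local: 1.0^0.5 = 1.000, no change.
- Both arms, alpha-global: 21^(0.5/46) = 1.034, about +3.4%, applied to all users alike. With 50 users it is 1.031, and with 23 it is 1.068.

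Global-arm users therefore shared one pattern that everyone's ratings moved slightly.

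**3. Share of use under own-rating weighting**

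Inputs: 46 participants (Results); two phases of three weeks (Study Design); triggered interventions from week 2 of P1 (App Intervention), so two intervention weeks in P1 and three in P2. The achieved split is not given. A 23/23 split is assumed from the planned maximum of 25 per group.

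- Person-phases: 23 / (46 × 2) = 23/92 = 25%.
- Intervention person-weeks: (23 × 3) / (46 × 5) = 69/230 = 30%.
- With 18 in the local arm (about 40:60): 18/92 = 20% and 54/230 = 23%.
- With 28 in the local arm (about 60:40): 28/92 = 30% and 84/230 = 37%.

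The share is below half in every case.

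**4. What averaging over P1 would do to the group effect**

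Let the true local-versus-global difference be δ in P2. By randomization the expected difference is 0 before it.

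- Weekly means, three weeks per phase with equal weight: (3 × 0 + 3 × δ)/6 = δ/2.
- Web questionnaire at T1, T2 and T3, where only T3 follows P2: (0 + 0 + δ)/3 = δ/3.

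These figures show what a group main effect over all points would estimate. The article does not say that this term will carry the hypothesis.

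**The case against.** The plan already keeps the two questions apart. Research Questions words the pre-post expectation as a result of using the prototype and links personalization to a separate hypothesis. Statistical Analysis repeats that separation. The abstract announces a two-factor mixed design, so group and time are both present. Limitations warns against firm attribution without a control group, and the article discloses several functions that were not achieved. All of this stands. The wording conflict in App Intervention remains, as does the need to say which contrast carries the personalization effect.

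A reader might also infer stronger points that the document does not support.

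- *That the abstract claims personalization in both phases.* There the mention of both phases governs recording stress and wearing the sensor. The next sentence, on algorithms, names no phase.
- *That every participant was said to have own-rating weighting in every week.* The App Intervention sentence speaks of a pattern forming over time, so 100% is not a fair comparator.
- *That most use was untailored apart from the decision tree.* Triggers from self-report and from individual sensor values ran from week 2 of P1 with no restriction by arm.
- *That the first hypothesis compares weighting with none.* A global-arm rating still moves the shared weights, and the article says openly that this arm would notice only small changes. It is a low-versus-high contrast, although the low side is shared rather than individual.
- *That the pooled result will be reported as an effect of personalization.* No passage says so; the risk lies in interpretation.

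**Conclusion.** The contradiction is in the current text. The statement that each person obtained an individualized pattern does not fit the global-arm setting in the same section, nor the account of P1 and the break. On the more specific passages, own-rating weighting applied to about 25% of person-phases or 30% of intervention person-weeks, with a range of about 20% to 37%. These shares rest on the assumed split and on the article's timing of the mechanisms. The 45% and 3.4% figures rest on the printed formulas at weight 0.5, and the second also on 46 users.

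The pre-post test remains usable for the stated hypothesis about using the prototype. Its pooled result is not evidence on individual weight learning. Within this design, that evidence comes from the randomized comparison of arms in P2.

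**What to change.** 1. Reconcile the App Intervention sentence on individualized patterns with Study Design, Randomization and the rest of App Intervention. Clarify the abstract and The Relax Approach section to match. The authors should confirm from the app's settings and logs what was delivered in P1 and in each arm of P2.
2. In the planned linear mixed models, treat P1, P2-global and P2-local as separate states and report the change for each.
3. Estimate the personalization effect as the randomized local-versus-global contrast in P2, not as a group main effect averaged over P1.
4. Describe the pooled pre-post change as change during use of the prototype, without attributing it to individualized weighting. Separate coding does not make the pre-post part causal: P2 also brought a third daily interval reminder and a sensor-data overview.

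The cost is some rewording and one factor in a model already planned, and the article says the analyses had not yet been run. The downside is a narrower claim from the pre-post result.

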### Data Collection

#### Overview

Data for the study were collected from 2 sources: the mandatory app and wearable sensor data collected as part of the Relax approach and instruments implemented specifically for the study.

Items for the primary and secondary outcomes from established instruments were translated into German where necessary. Table 1 shows an overview of all outcomes, and Table 2 shows the data collection during the course of the study.

**Table 1 table1:** Primary and secondary outcomes and their measurement conditions.

Outcome			Subscales		Design of measurement		Instrument		Item format		Example item
**Primary**											
	Momentary emotional state	Arousal, valence		Daily EMA^a^ (morning, interval)		Internally created scale		7-point Likert scale		“My current mood is:”	
	Emotional state of last stress event	Arousal, valence		Daily EMA (interval)		Internally created scale		7-point Likert scale		“My mood was:”	
	Chronic stress	Lack of satisfaction, high demand, loss of control, ability to recover, and negative emotions		Daily EMA (interval)		Selected items from CSSS^b^ [53] and LKCS^c^ [54]		7-point Likert scale		“I couldn’t relax today.”	
	Work-related distress	Relationship, personal accountability, work-life balance, and workload		Pre-post online		VEDAS^d^ [55], online		6-point Likert scale		“Dealing with ambiguous or ‘delicate’ situations.”^e^	
	Work-related eustress	Relationship, personal accountability, work-life-balance, and workload		Pre-post online		VEDAS [55], online		6-point Likert scale		“Dealing with ambiguous or ‘delicate’ situations.”^e^	
	Satisfaction	Overall satisfaction, workday adaptability, exertion due to EMA, and exertion due to sensor handling		Pre-post online		CSAT^f^ [56], internally extended), online		5-point Likert scale		“How would you rate your overall satisfaction with Relax?”	
	Usability	—		Pre-post online		SUS^g^ [57], online		5-point Likert scale		“I found using the Relax app unnecessarily complicated.”	
	HRV^h^	SDRR^i^, RMSDD^j^, and LF^k^/HF^l^		Continuously		Polar VS^m^		Passive		—^n^	
**Secondary**											
	Momentary activity	Environment (work or private), type of activity (if work: routine or extraordinary, if private: duty or leisure), physical exertion, mental exertion, and social activity		Daily EMA (interval)		Internally created scale		Dichotomous, 7-point Likert scale, single choice, open (text)		“Is work time right now?”	
	Activity of last stress event	Physical exertion, mental exertion		Daily EMA (interval)		Internally created scale		7-point Likert scale		“My physical exertion was:”	
	Expected stress	—		Daily EMA (morning)		Internally created scale		7-point Likert scale		“I expect for today:”	
	Subjective sleep quality	Subjective restfulness, sleep disruptions		Daily EMA (morning)		Internally created scale		7-point Likert scale, dichotomous, open (numeric)		“My sleep was:”	
	Summarized emotional state	Arousal, valence		Daily EMA (evening)		Internally created scale		7-point Likert scale		“My general mood throughout the day was:”	
	Summarized well-being	—		Daily EMA (evening)		Internally created scale		7-point Likert scale		“I felt overall today:”	
	Summarized activity	Environment (work/private), type of activity (if work: routine/extraordinary; if private: duty/leisure), physical exertion, and mental exertion		Daily EMA (evening)		Internally created scale		Dichotomous, 7-point Likert scale		“Has today been a workday?”	
	User feedback	Sensor handling, favorite function, requests on functionality, and general feedback		Pre-post online		Internally created scale		Open (text)		“What were your favorite features of the Relax app?”	
	Acceptable price	Optimal price, indifference price, marginal cheapness, marginal expensiveness		Pre-post online		PSM^o^ [58]		Open (numeric)		“At what price would the product on a monthly subscription basis be too expensive for you to buy it?”	
	Physical arousal	Mean HR^p^ and mean RR^q^		Continuously		Polar VS		Passive		—	

^a^EMA: Ecological Momentary Assessment.

^b^CSSS: Chronic Stress Screening Scale.

^c^LKCS: Leipzig Screening Questionnaire on Chronic Stress.

^d^VEDAS: Valencia Eustress-Distress Appraisal Scale.

^e^In the VEDAS, the same items were presented twice, once with a eustress framing of the instruction and once with a distress framing.

^f^CSAT: customer satisfaction score.

^g^SUS: System Usability Scale.

^h^HRV: heart rate variability.

^i^SDRR: SD of r-r-intervals.

^j^RMSSD: root mean square of successive differences.

^k^LF: low frequency.

^l^HF: high frequency.

^m^VS: Verity Sense. The same items were presented twice, once with a eustress framing of the instruction and once with a distress framing.

^n^Not applicable.

^o^PSM: price sensitivity meter.

^p^HR: heart rate.

^q^RR: r-r-intervals.

**Table 2 table2:** Study schedule of enrollment, interventions, and assessments, according to the SPIRIT (Standard Protocol Items: Recommendations for Interventional Trials) guidelines [59].

Time point		Study period					
		Enrollment	Preallocation		Allocation	Postallocation	
		T0^a^	T1^b^	P1^c^	T2^d^	P2^e^	T3^f^
